**3.4 VE exposure**

**Definition**

Patients will be defined as vaccinated if they have received the 2022/23 seasonal vaccine at least 14 days before the date of the swab. Note that 2 doses of LAIV are recommended for some children, but will be considered vaccinated from 14 days after the first dose.

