**3.6 VE exclusion criteria**

Registered patients may be excluded if they have expressed a wish to be excluded from the surveillance programme; or opted out of sharing their data. However, those who consent to a virology swab will include in their consent record sharing for this purpose.

We ideally look for swabs to fall within 0-7 days of reported illness onset. However, patients will not be excluded where no onset date is given or if the number of days between onset and swab exceeds 7 days (the impact of missing and longer onsets will be explored and multiple imputation methods used). Swabs with implausible onset dates post sample receipt will be retained and the onset date replaced as missing.

Patients must have both a negative influenza A and an influenza B result present to be included as a control.

Patients with nonsensical vaccination histories (e.g. outside the flu season, adults that received LAIV, children that received aQIV) or swab dates (e.g. if swabbed after date of receipt) will be excluded, as will swabs received >21days after the reported date taken.

The study will include only those with known age between 2 and 105 and known sex.

Patients residing outside the boundaries of their respective schemes will be excluded i.e. RCGP/UKHSA patients must be resident in England, PHS patients must be resident in Scotland.

Patients with unknown vaccination status will be excluded. This will include patients with no linkage to either NIMS or a GP record in England, and patients for whom no definite yes/no response to the question on vaccination status was recorded on the Welsh swabbing form. Scottish patients will be assumed to be unvaccinated if no record of vaccination is found.

LAIV-eligible patients aged 2-17 will be excluded if they were vaccinated 0-20 days before symptom onset, or if no vaccination date is available, to ensure positives are not related to LAIV. Patients aged 18+ will not be considered fully vaccinated until 14-days post vaccination. Those swabbed during days 1-13 post vaccination will be included in analyses and assigned a separate exposure category for recent vaccination. Vaccinated adults aged 18+ will not be excluded if no vaccination date is available, instead a multiple imputation approach will be used.

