**Flu and RSV descriptive analyses**

Cases and non-cases will be described according to:

- Month of swab – count (%)
- Sex – count (%)
- Age group – count (%)
- Region - count (%)
- Risk status – count (%)
- Vaccination Status including Vaccination Type – count (%)
- Past season vaccination status – count (%)
- COVID-19 vaccination status – count (%)

Differences in swab positivity within these groups will be tested using Chi-squared or Fisher’s exact test, as appropriate. Swabs with a gap from onset to swab >7d, and swabs taken less than 14days (21days for children) of vaccination will not be included in descriptive analyses.

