**Missing data**

We will aim to use multiple imputation methods for our main analysis where possible, rather than exclude data. However, data on vaccination status, age group and date of swab must be complete for inclusion in the study.

*Multiple imputation for missing risk status*

Multiple imputation methods will be used for missing data on risk status, taking into account patient age, and vaccination history and age eligibility.

*Multiple imputation for missing onset date*

Multiple imputation will be used where onset dates are missing. An interaction term between vaccination status and indicator for swab within 0-7days of onset will fitted (the sample size needs to remain consistent). Where onset is missing this indicator will be imputed based on the proportion of samples with known onset falling within the 7day window, taking into account positivity for flu or other viruses and patient age.

*Multiple imputation for missing vaccination date*

Where an adult patient has indicated that they were vaccinated at the time of the swab, but no vaccination date was given, a hot-deck imputation approach will be used. Vaccination dates will be sampled from other vaccinated patients within the same broad age cohort (18-64 or 65+) and swabbed within the same week. The imputed vaccination dates will be used to assign patients as within 1-13 days of vaccination or fully vaccinated.

In secondary analyses by vaccine type, a category for unknown vaccine type will be included. (Since vaccine type is almost universally missing for patients whose vaccination date is missing, the above imputation approach for vaccination dates need not be taken for analyses of vaccine type).

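### Study 2: the LAIV exclusion for children is counted to symptom onset, so it cannot be applied when onset is missing and does not cover vaccination between onset and swab

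*Protocol*

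**What the plan says.** All references are to Study 2 of the protocol.

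- **Section 3.4, Definition.** A patient is vaccinated if the dose was given "at least 14 days before the date of the swab". Children for whom two LAIV doses are recommended "will be considered vaccinated from 14 days after the first dose".
- **Section 3.6, exclusion.** "LAIV-eligible patients aged 2-17 will be excluded if they were vaccinated 0-20 days before symptom onset"; those with no vaccination date are excluded too. The stated purpose is "to ensure positives are not related to LAIV".
- **Section 3.6, missing onset.** Elsewhere in the section, "patients will not be excluded where no onset date is given". In addition, "Swabs with implausible onset dates post sample receipt will be retained and the onset date replaced as missing".
- **Section 3.10, Missing data.** "Where onset is missing this indicator will be imputed based on the proportion of samples with known onset falling within the 7day window". No onset date is imputed.
- **Section 3.10, descriptive analyses.** "swabs taken less than 14days (21days for children) of vaccination will not be included in descriptive analyses".
- **Section 3.8, Table 1.** The influenza PCR field has a separate code, #laiv, for detected LAIV strains. Section 3.5 defines a case by a positive influenza test and does not mention this code.
- **Section 3.10, sensitivity analyses.** The first one drops patients with unknown onset.

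**The concern.** Whether a positive swab reflects vaccine virus depends on the time from vaccination to swab. The section 3.6 exclusion instead runs from vaccination to onset, a date that the same section allows to be absent. Two groups pass through: children with no usable onset date, and children vaccinated between onset and swab, since their dose did not precede onset.

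VE in ages 2-17, split by nasal and inactivated vaccine, is among the primary objectives (section 2.2). Most primary-school vaccination takes place from October to December, inside the study period, and an early estimate is due before the February 2024 WHO meeting (section 3.3). A vaccine-strain detection counted as influenza biases the LAIV estimate, in a direction that depends on the exposure group to which the child is assigned.

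**Working it through.** The plan gives no figure to reproduce. The check has two parts: applying the rules to each type of child, then an illustration of size.

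**1. Applying the rules.** Let v be days from vaccination to swab and g days from onset to swab.

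- Section 3.4: vaccinated if v ≥ 14.
- Section 3.6: excluded if 0 ≤ v − g ≤ 20; cannot be evaluated if g is missing.
- Section 3.10, descriptive tables, children: dropped if v < 21.

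| Child | 3.6 exclusion | 3.4 status | Descriptive interval rule |
|---|---|---|---|
| Onset known, g = 0, v = 14-20 | excluded | not needed | dropped |
| Onset known, g = 7, v = 21-27 | excluded | not needed | kept |
| Onset known, g = 7, v = 0-6 (vaccinated after onset) | not excluded, since v − g < 0 | not vaccinated | dropped |
| Onset missing, v = 14-20 | cannot be applied | vaccinated | dropped |
| Onset missing, v = 0-13 | cannot be applied | not vaccinated | dropped |

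The last three rows are the gap: the child is in the VE analysis although swabbed within 21 days of vaccination. In the fourth row the child counts as vaccinated.

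In the third and fifth rows the exposure category is unclear. Section 3.6 has a separate recent-vaccination category for days 1-13, but introduces it directly after a sentence about patients aged 18 and over. If it covers children too, days 1-13 stay out of both main groups. If it does not, they may fall into the unvaccinated reference group.

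**2. Illustrative size.** Every input here is an assumption, because the documents give neither the proportion with missing onset nor a LAIV detection rate.

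- True VE 50%; positivity in unvaccinated children 15%, so odds = 0.15/0.85 = 0.1765.
- Vaccinated odds = 0.5 × 0.1765 = 0.0882, so p1 = 0.0882/1.0882 = 0.0811.
- Share s of vaccinated-child swabs affected: about 5% at days 14-20, of which 10-30% lack onset. This gives 0.05 × 0.10 = 0.5% to 0.05 × 0.30 = 1.5%.
- Vaccine-strain positivity f in that group: 5-20%.
- Formula: p1′ = p1 + s·f·(1 − p1); VE = 1 − [p1′/(1 − p1′)]/0.1765.

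Results for children counted as vaccinated:

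- s = 0.5%, f = 5%: p1′ = 0.0813, odds 0.0885, VE 49.8%.
- s = 1.5%, f = 20%: p1′ = 0.0838, odds 0.0915, VE 48.1%.

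The loss is about 0.2 to 1.9 points.

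For the opposite direction, suppose children at days 0-13 are counted as unvaccinated and make up the same 0.5-1.5% of that group (a further assumption). Then p0′ = 0.15 + s·f·0.85, and VE = 1 − 0.0882/[p0′/(1 − p0′)]. At s = 0.5%, f = 5%, p0′ = 0.1502 and VE is 50.1%; at s = 1.5%, f = 20%, p0′ = 0.1526 and VE is 51.0%.

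**The case against.** **The rules need not conflict.** A reader might infer that sections 3.4, 3.6 and 3.10 give three incompatible rules for the same child. The documents do not support that. Section 3.6 decides who enters the VE analysis and section 3.4 classifies those who remain; with onset known, they work in sequence. The LAIV sentence in 3.4 mainly settles whether one or two doses are required. The 21-day swab rule is limited to descriptive tables, which also drop swabs taken more than 7 days after onset, so those denominators differ from the VE analysis by design. This objection stands, but does not help where onset is missing.

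**The bias is not all downward.** This also stands. Only missing-onset children at days 14-20 are clearly counted as vaccinated. The schemes indicate swabbing within 7 or 10 days of onset (sections 3.2 and 3.5), so a child vaccinated after onset is normally under day 14 at the swab and not vaccinated under 3.4.

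**Safeguards exist.** The #laiv code is a PCR result code, and nothing says it is available only for genetically characterised samples. Section 3.6 promises to explore the impact of missing onset, and a sensitivity analysis drops unknown onsets. These reduce the concern without closing the gap: no rule says how #laiv results are classified, the main analysis keeps the affected children, and dropping unknown onsets does nothing for a child with a known onset who was vaccinated after it.

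**A SAP could supply the fallback.** Possibly. But the protocol already fixes the exclusion, its anchor date and the retention of missing onsets, and as written these defeat the purpose stated in section 3.6.

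**Conclusion.** The point holds for a defined group. As written, the plan admits to the VE analysis children with missing onset swabbed within 21 days of vaccination, and children vaccinated between onset and swab. A vaccine-strain positive lowers VE if the child is at days 14-20 and counted as vaccinated; it would raise VE if the child is at days 0-13 and counted as unvaccinated.

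The size cannot be computed from the documents. Under the assumptions shown it is about 0-2 VE points downward, with up to about 1 point upward possible from the other group. A reader might infer a much larger fall: with s = 10% and f = 20%, the same formula gives p1′ = 0.0995, odds 0.1104 and VE of 37%. Nothing in the documents supports a share that high, and it would require far more children than the missing-onset group at days 14-20 is likely to contain.

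The plan should still be changed, because a stated rule fails its own purpose in an age group with a primary objective and the correction is simple.

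**What to change.** 1. **Section 3.6.** Exclude LAIV-eligible children aged 2-17 vaccinated 0-20 days before the swab, in addition to those vaccinated 0-20 days before a known onset. Section 3.10 requires the swab date to be complete, and section 3.6 already excludes these children if the vaccination date is missing, so the rule can always be applied. It matches the 21-day window already used for children in the descriptive tables. With onset missing it removes v = 0-20; with g = 7 it removes v = 0-27, including doses given after onset.
2. **Sections 3.5 and 3.6.** State that #laiv results are not counted as influenza cases.
3. **Section 3.4.** Cross-refer to the exclusion. Keep the 14-day definition for adults, and for children who are not LAIV-eligible or who received inactivated vaccine and are not otherwise excluded. Restricting it to adults would leave those children with no definition of vaccinated.
4. **Section 3.8.** Where exact vaccination dates are replaced by day-threshold indicators, say that these are counted to the swab date, so that the swab-based exclusion can be applied.

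The cost is short wording changes, one additional filter and the loss of a small number of child swabs.

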**De-duplication**

It is important to ensure that each individual positive episode is included only once, but given that a patient may experience multiple influenza episodes each season, patients may contribute more than one swab to the study, if swabs can reasonably be considered independent.

Patients who had had more than one test can be included as cases and controls more than once, unless the tests were within 28 days. For repeat tests within 28 days, the second test will be excluded, unless a positive test came after a negative test, in which case the negative result will be excluded.

**3.7 Sub-groups**

**Risk groups**

Study subjects are categorised according to Department of Health defined risk categories for influenza vaccination. High risk is determined by the presence of well recognised risk morbidities recorded in the electronic health record for the patient concerned.

- Underlying heart disease
- Chronic respiratory disease
- Diabetes mellitus
- Chronic kidney disease
- Chronic neurological disease
- Splenic dysfunction
- Immunosuppression
- Morbid obesity (BMI>40)
- Chronic liver disease

**Currently pregnant**

- Pregnancy

**Previous vaccination**

Influenza vaccination in the previous season (2022/23)

**Virus genetic characterisation**

Virus clade, and for influenza B lineage

**3.8 Data items**

Most data items are available through electronic health or laboratory records. Some data items are collected by the GPs in their GP practice (or by individuals if self-swabbing) and entered onto a swab questionnaire.

**Table 1: Data items requested**

| **Column** | **Responses** | **Explanation** |
| --- | --- | --- |
|  |  |  |
| Year |  | Year of sample |
|  |  |  |
| Lab_Number |  | Local unique laboratory number |
|  |  |  |
| RECEIPT_DATE | dd/mm/yyyy | Date of sample receipt by lab |
|  |  |  |
| SAMPLE_DATE | dd/mm/yyyy | Date sample taken |
|  |  |  |
| ONSET_DATE | dd/mm/yyyy | Date of onset of illness |
|  |  |  |
| PRESENCE_OF_FEVER | #inp | Not completed on form |
|  | No | No |
|  | Not known | Not known |
|  | Yes | Yes - fever >38 degrees with onset in previous 7 days |
|  |  |  |
| PRESENCE_OF_COUGH | #inp | Not completed on form |
|  | No | No |
|  | Not known | Not known |
|  | Yes | Yes - cough with onset in previous 7 days |
|  |  |  |
| PRESENCE_OF_LOSS_OF_TASTE_OR_SMELL | #inp | Not completed on form |
|  | No | No |
|  | Not known | Not known |
|  | Yes | Yes - cough with onset in previous 7 days |
|  |  |  |
| PRESENCE_OF_SHORTNESS OF BREATH | #inp | Not completed on form |
|  | No | No |
|  | Not known | Not known |
|  | Yes | Yes - SOB with onset in previous 7 days |
|  |  |  |
| PRESENCE_OF_WHEEZE (<5 year) | #inp | Not completed on form |
|  | No | No |
|  | Not known | Not known |
|  | Yes | Yes - wheeze with onset in previous 7 days |
|  |  |  |
| Individual_ID |  | Pseudonomised Individual Identifier |
|  |  |  |
| SEX | m | male |
|  | f | female |
|  | nk | non known |
|  |  |  |
| DATE_OF_BIRTH | dd/mm/yyyy | Date of birth |
|  |  |  |
| CMO_RISKGRP | #inp | Not completed on form |
|  | No | No |
|  | Not known | Not known |
|  | Yes | Yes |
|  |  |  |
| Seasonal_Vaccine_date_23_24 | dd/mm/yyyy | Date of vaccination |
|  |  |  |
| Seasonal_Vaccination_23_24 | #inp | Not completed on form |
|  | Yes | Vaccinated |
|  | nk | Not known |
|  | No | Not vaccinated |
|  |  |  |
| Vaccination_Route_23_24 | #inp | Not completed on form |
|  | Intramusuclar | Vaccinated |
|  | Intranasal | Not known |
|  | nk | Not known |
|  |  |  |
| Vaccine_Type_23_24 | LAIV | LAIV |
|  | aQIV | QIV - adjuvanted |
|  | QIVr | QIV - recombinant |
|  | QIVe | QIV - egg based |
|  | QIVc | QIV - cell based |
|  | nk | Not known |
|  | #inp | Not completed on form |
|  |  |  |
| Past_Seasonal_Vaccination_22_23 | #inp | Not completed on form |
|  | nk | Not known |
|  | Yes | Vaccinated |
|  | No | Not vaccinated |
|  |  |  |
| COVID19_Autumn23_Vaccine_Date | dd/mm/yyyy | Date of any COVID19 vaccination since Sept 2023 |
|  |  |  |
| COVID19_Autumn23_Vaccination | #inp | Not completed on form |
|  | nk | Not known |
|  | Yes | Vaccinated since Sept 2023 |
|  | No | Not vaccinated |
|  |  |  |
| FLU_PCR_Result | #flub | Influenza B |
|  | #h1 | Influenza AH1 |
|  | #h3 | Influenza AH3 |
|  | #flua | Influenza A(unknown) |
|  | #h1h3 | Influenza AH1 AND influenza AH3 |
|  | #h1h3flub | Influenza AH1 AND influenza AH3 AND influenza B |
|  | #h3flub | Influenza AH3 AND influenza B |
|  | #h1flub | Influenza AH1 AND influenza B |
|  | #laiv | LAIV strains detected |
|  | #nvd | No virus detected |
|  |  |  |
| Other_PCR_Result | #covid | SARS-CoV-2 |
|  | #hmpv | Human Metapneumavirus |
|  | #ra | RSV A |
|  | #rb | RSV B |
|  | #rarb | Both RSV A and RSV B detected |
|  | #rsv | RSV untyped |
|  | #adeno | Adenovirus |
|  | #rhino | Rhinovirus |
|  | #corona | Seasonal coronavirus |
|  | #nvd | No virus detected |
|  |  |  |
| Final_Overall_Result | #b,#nvd | Influenza B |
|  | #h3,#nvd | Influenza AH3 |
|  | #h1,#nvd | Influenza AH1 |
|  | #nvd,#covid | SARS-CoV-2 |
|  | #nvd,#hmpv | Human Metapneumavirus |
|  | #nvd,#ra | RSV A |
|  | #nvd,#rb | RSV B |
|  | #nvd,#rarb | Both RSV A and RSV B detected |
|  | #nvd | No virus detected |
|  | Results awaited | Results awaited |

Some of the above data items above are not essential to the main study, such as symptom information, these may be used if there is specific interest in symptom groups or to exclude those with COVID19-like illness. The level of detail could be lessened to enable data sharing, e.g. age on 1^st^ September 2023 can be given instead of DOB, indication that vaccination was given ≥0, 14 and 21 days prior rather than precise vaccination dates, lab number can be pseudonymised.

Further genetic characterisation data is requested, where available, for the 2022/23 season circulating strains of interest include:

| genetic group | Like virus | amino acid substitutions |
| --- | --- | --- |
| H1N1 |  |  |
| 6B.1A.5a.2 | A/Victoria/2570/2019 (vaccine) | K130N, N156K, L161I, V250A |
| 6B.1A.5a.2a | A/Sydney/5/2021 | K54Q, A186T, Q189E, E224A, R259K, K308R |
| 6B.1A.5a.2a.1 | A/Norway/25089/2022 | P137S, K142R, D260E |
| 6B.1A.5a.1 | A/Guangdong-Maonan/SWL1536/2019 |  |
| H3N2 |  |  |
| 3C.2a1b.2a.2 | A/Bangladesh/4005/2020 | Y159N, T160I, L164Q, G186D, D190N, Y195F |
| 3C.2a1b.2a.2a | A/Darwin/9/2021 (vaccine) | H156S |
| 3C.2a1b.2a.2a.1 | A/Slovenia/8720/2022 | D53G, D104G, K276R |
| 3C.2a1b.2a.2a.1a |  | L157I, K220R |
| 3C.2a1b.2a.2a.1b | A/Catalonia/NSVH161512067/2022 | I140K, R299K |
| 3C.2a1b.2a.2a.2 | A/Poland/97/2022 | D53G, R201L, S219Y |
| 3C.2a1b.2a.2a.3 | A/Norway/24873/2021 | D53N, N96S, I192F |
| 3C.2a1b.2a.2a.3a |  | E50K |
| 3C.2a1b.2a.2a.3a.1 |  | I140K |
| 3C.2a1b.2a.2a.3b |  | I140M |
| 3C.2a1b.2a.2b | A/Thuringen/10/2022 | E50K, F79V, I140K |
| 3C.2a1b.2a.2c |  | S205F, A212T |
| 3C.2a1b.2a.2d |  | G62R, H156Q, S199P |
| 3C.2a1b.2a.1a | A/Cambodia/e0826360/2020 |  |
| B |  |  |
| V1A.3a.2 | B/Austria/1359417/2021 (vaccine) | A127T, P144L, K302R |
| V1A.3a.2 (i) |  | T182A, D197E, T221A |
| V1A.3a.2 (ii) |  | E128K, A154E, S208P |
| V1A.3a.2 (iii) |  | E198G |
| V1A.3a.2 (iv) |  | D129G, D197E |
| V1A.3a.2 (v) |  | R80G, E184K |
| V1A.3a.2 (vi) |  | E183K |

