In recent seasons, it has become apparent that the current inactivated influenza vaccine programme provides sub-optimal protection to the age-groups >65 years of age, especially against influenza A/H3N2. Adjuvanted vaccines have been preferentially recommended since the 2018/19 season to all in this age-group. Since 2019/20, cell-based quadrivalent vaccines have also been available and used preferentially over standard-dose egg-based vaccines. The recombinant vaccine has also been available since 2021/22, though uptake has been low. In addition, all adults 50-64 years of age have been eligible to receive either cell or egg-based quadrivalent influenza vaccines since the 2020/21 season with the aim of reducing pressure on the health service during the COVID-19 pandemic. It is thus critically important to obtain accurate estimates of the relative effectiveness of these influenza vaccines in the relevant age groups targeted with different vaccine types (2-17, 18-64, 65+), and bringing together data from across the UK will help this aim. This proposal concerns the use of the test-negative case control method to estimate influenza vaccine effectiveness using the various UK sentinel GP swabbing schemes, with a particular focus on the absolute and relative effectiveness of these vaccines.

Further, some influenza positive sentinel swabs are targeted for genetic characterisation. Exploring vaccine effectiveness by sub-clade may help us better understand the impact of antigenic drift on vaccine effectiveness and inform vaccine strain selection. Bringing together this information from sentinel schemes across the UK helps maximise our potential to produce vaccine effectiveness estimates by sub-clade and optimize use of this valuable data.

Finally, a number of RSV vaccines are approaching licensure. There is a need to establish systems to monitor the baseline epidemiology of RSV prior to introduction of these vaccines and for this to then provide a platform to monitor the RSV vaccine programme impact and effectiveness. The burden of disease due to RSV is increasingly being recognised – particularly in young infants and also potentially the elderly, though questions remain. There is a need to establish RSV disease burden in the UK, particularly in younger children and the elderly to inform optimal future use of these new vaccines and to provide a baseline for subsequent impact studies stage.

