**2. Aim and Objectives**

**2.1 Aim**

For the 2023/24 season, the aims are to:

- Estimate the pooled influenza vaccine effectiveness for laboratory confirmed infection in primary care across three age groups: children aged 2-17, working-age adults 18-64 and the elderly aged 65+ in the UK.
- Monitor RSV epidemiology in primary care with a focus on children <5 years of age

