**3. Methods**

**3.1 Study designs**

- Test-negative case-control (TNCC) design will be used to estimate VE.
- For RSV descriptive statistics on swab positivity will be collated, by age group, gender, month and risk status.

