**3.3 Study period**

The start of the influenza vaccination campaign is usually in mid-September as soon as influenza vaccine becomes available. It is theoretically available until supplies run out, although the bulk is delivered in late September through to November. The bulk of childhood vaccinations in Primary schools are delivered October to December.

The study period will commence from 4 September 2023 (the point when influenza vaccination rollout and influenza and RSV transmission may begin) and continue for the duration of the UK influenza season. An early calculation of VE will be performed prior to the February 2024 WHO strain selection committee meeting, with a full analysis carried out at the end of the season.

This proposal relates to an ongoing programme of disease surveillance. The end of the influenza season is not fixed *a priori*. The period of influenza activity is determined using data from the national influenza surveillance system.

RSV statistics will be collated at the end of the influenza season using the same season definition as for influenza.

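### Study 2 lets a scheme give age on 1 September 2023 instead of date of birth, which leaves infants born during the study without a valid age for the RSV description by age group

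*Protocol*

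**What the plan says.** All references are to Study 2 of the Protocol.

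- Section 3.8, Table 1 requests full date of birth: "DATE_OF_BIRTH | dd/mm/yyyy | Date of birth".
- The note below the table relaxes this. "The level of detail could be lessened to enable data sharing", it says, and the first example is that age on 1 "September 2023 can be given instead of DOB". The note gives no unit for that age and no code for a child born after the date.
- Section 3.3: "The study period will commence from 4 September 2023". For RSV the window is the same: "RSV statistics will be collated at the end of the influenza season using the same season definition as for influenza". The end of the season is not fixed in advance.
- Section 2.1 gives one aim as "Monitor RSV epidemiology in primary care with a focus on children <5 years of age". Section 2.2 lists a description of RSV in children among the primary objectives.
- Section 3.1 sets the analysis: "For RSV descriptive statistics on swab positivity will be collated, by age group, gender, month and risk status". It gives no age bands.
- Section 1 says that the RSV burden is increasingly recognised, "particularly in young infants and also potentially the elderly", and asks for a baseline before RSV vaccines are introduced.
- Section 3.10, under Missing data, makes a complete age group a condition of inclusion.
- Section 3.6, headed as exclusion criteria for vaccine effectiveness, limits the study to ages 2 to 105.

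**The concern.** A fixed reference date at the start of the season suits influenza vaccine eligibility. It does not suit RSV in infancy, where age changes materially within one season. The reference date falls three days before the study opens, so every child born during the study is born after it, and age on that date is negative or undefined for them. For every other child the recorded age is too low by the time from 1 September to the swab.

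What is at stake is the RSV description by age group in any scheme that uses the option. Season-born infants could be left out if the scheme returns a blank and the completeness rule for age group is applied. If they are kept with a nominal age of 0, they share a band with children well past their first birthday. In either case that scheme's youngest bands would not be comparable with those of schemes supplying date of birth, and the baseline would be weaker in an age range that the background singles out.

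**Working it through.** The Protocol states no figure on this point, so there is none to reproduce. The check is date arithmetic.

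**Inputs.** Reference date 1 September 2023 (note under Table 1). Study start 4 September 2023 (section 3.3). Assumption, not in the Protocol: births are even over time.

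**Step 1: share without a valid age on a given day.** For an age band of width w days, with t days since 1 September 2023, the share of children in the band who were born after the reference date is min(1, t/w).

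| Swab date | t (days) | Under 1 (w = 365.25) | Under 5 (w = 1826.25) |
|---|---|---|---|
| 1 December 2023 | 30 + 31 + 30 = 91 | 91/365.25 = 24.9% | 91/1826.25 = 5.0% |
| 1 January 2024 | 91 + 31 = 122 | 122/365.25 = 33.4% | 122/1826.25 = 6.7% |
| 1 March 2024 | 122 + 31 + 29 = 182 | 182/365.25 = 49.8% | 182/1826.25 = 10.0% |

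On these dates every infant under about 3, 4 and 6 months respectively was born after the reference date.

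**Step 2: average over the season.** The figures above are for single days. Averaging min(1, t/w) over all days from 4 September, with an even swab rate over time and age (a further assumption), and three assumed season ends because the Protocol fixes none:

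| Age at swab | To 31 Dec 2023 | To 31 Mar 2024 | To 19 May 2024 |
|---|---|---|---|
| Under 6 months | 34% | 58% | 66% |
| Under 12 months | 17% | 29% | 36% |
| Under 5 years | 3% | 6% | 7% |

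**Step 3: does coding these infants as 0 solve it?** A child aged 0 on 1 September 2023 was born in the preceding 12 months. On 1 March 2024 that child is about 6 to 18 months old, so the recorded under-1 band contains nobody under 6 months, and about half of it (182/365.25) is past 12 months. Adding season-born infants as 0 gives a band running from birth to about 18 months. The upper limit moves too: children recorded as under 5 are by then up to about 5.5 years old.

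**Step 4: which analyses are touched.** The RSV description by age group is. Influenza vaccine effectiveness is estimated from age 2 upwards, so season-born infants do not enter it and their missing ages have no effect there.

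**The case against.** The strongest reply is that this is an optional relaxation, offered as an example. Date of birth remains the requested item, and no section says that any scheme will use the substitute. That stands, and it makes the whole point conditional.

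A reader might infer that the plan drops season-born infants from the RSV description. The text does not say so. Section 3.10 requires age group, not exact age, and a child born after 1 September 2023 and swabbed this season can be placed in the youngest group if the scheme returns 0, a negative value or a flag. Loss needs a blank return and an analyst who discards it. What remains is that the Protocol gives no coding rule, and that placing these children at 0 leaves the mixed band shown in step 3.

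A reader might also infer that the study ranks young infants as its most important RSV group. It does not: the background also names the elderly, the aim is children under 5, and the objective is children generally.

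The missing band definitions cut both ways. With one band for all under-5s the effect is small, 3% to 7% averaged over the season. The sample date is also still requested, so age on 1 September given in months could be rolled forward to the swab date. The note does not ask for months, however, and completed years cannot be rolled forward.

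Finally, the limit of ages 2 to 105 in section 3.6, read literally, removes these infants whichever age field is supplied. But that limit sits under a heading on vaccine effectiveness and conflicts with the under-5 RSV aim if applied to RSV. It does not make the substitute field suitable.

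**Conclusion.** The point holds in a conditional and minor form. Where a scheme supplies age on 1 September 2023 instead of date of birth, infants born during the study have no valid age, other children are recorded as younger than at swab, and the RSV description by age group may lose or misclassify the youngest children.

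The share without a valid age reaches about half of under-1s and a tenth of under-5s by 1 March 2024. Averaged over the season it is 17% to 36% of under-1s, depending on the season end. These shares rest on even births and, for the averages, on even swabbing. They apply only within schemes that use the option, and they count children without a valid age, not children excluded. The documents do not show that any scheme will use the option or that any child will be dropped.

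**What to change.** Change the example in the note under Table 1. Where date of birth cannot be shared, request age at swab: completed months for children under 5, or bands such as 0–2, 3–5, 6–11, 12–23 and 24–59 months, and years above that. Keep age on 1 September 2023 only as an added field for vaccine eligibility.

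At the same time, reconcile section 3.6 with section 2.1 by stating that the 2 to 105 age limit applies to the vaccine effectiveness analysis only. Without that, the better age field does not help the RSV description for children under 2.

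The cost is one changed line in the data request and one clarifying phrase in section 3.6. Slightly more age detail is shared for young children, which banding limits.
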